## **7.2 Treatment after Surgery**

Standard postoperative treatment consisted of 0.3% tobramycin/dexamethasone (TobraDex, Alcon) eyedrops, 0.5% levofloxacin (Cravit, Santen) eyedrops and sodium hyaluronate (HYCOSAN, URSAPHARM Arzneimittel GmbH) four times a day for one week. Tobradex and Cravit were suspended after one week, but artificial tear eyedrops were applied as required until one month.

## **7.3 Clinical Assessments**

### **7.3.1 Corneal Central Sensitivity (CCS)**

Corneal central sensitivity is measured with a Cochet-Bonnet esthesiometer (Luneau, Paris, France). This instrument consists of a nylon monofilament that is 60 mm in length and with diameter of 0.12 mm. The instrument is advanced perpendicular to the central surface of the cornea until contact between the instrument and the cornea is made. If the patient feels the filament, the response is defined positive. Corneal central sensitivity is tested three times with each filament length, and the length of the filament is sequentially reduced from 60 mm in 5-mm steps. At least two positive responses among three attempts are considered a positive result at each filament length. The longest filament length that resulted in a positive result is considered the corneal threshold. This evaluation will just be performed at baseline, 1 week and 1 month after surgery in order to avoid the potential for corneal damage at 1 day postoperatively.

### **7.3.2 Schirmer I Test (SIT)**

The Schirmer test without anesthesia (SIT) for tear secretion function will be performed by inserting a 30-mm Schirmer tear test strip (Jingming, Tianjing, China) into the inferior fornix at the junction of the middle and lateral thirds of the lower eyelid margin. Schirmer test strips will remain in place for 5 minutes with the eyes closed. The extent of wetting will be subsequently measured according to the scale provided by the manufacturer. Potential scores ranged from 0 to 30 mm, with lower scores indicating greater tear production abnormalities. This evaluation will be performed at baseline, 1 day, 1 week and 1 month after surgery.

### **7.3.3 Corneal Fluorescein Staining (FL)**

Upper, lower, nasal, temporal and central quadrants were used. Superficial punctate keratopathy (SPK) in the cornea was scored from 0 to 3 in each quadrant: 0, no staining in the cornea; 1,  $<5$  punctuate stains; 2,  $>5$  punctuate stains but  $<10$ ; and 3,  $>10$  or filamentous staining detected. The total number was obtained by adding the scores of the four quadrants for each eye (0–15). This evaluation will just be performed at baseline, 1 week and 1 month after surgery in order to avoid the potential for corneal damage at 1 day postoperatively.

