## **3 STUDY OBJECTIVES**

### **3.1 Primary Objective**

3.1.1.Determine the changes of ocular surface including central corneal sensitivity, Schirmer I test (SIT), noninvasive tear breakup time (NI-TBUT), tear meniscus height, corneal fluorescein (FL) staining, ocular surface disease index (OSDI) of the two surgeries preoperatively and postoperatively

3.1.2.Evaluation the changes of tear concentrations of interleukin- $1\alpha$  (IL- $1\alpha$ ), tumor necrosis factor- $\alpha$  (TNF- $\alpha$ ), nerve growth factor (NGF), interferon- $\gamma$  (IFN- $\gamma$ ), transforming growth factor- $\beta 1$  (TGF- $\beta 1$ ) and matrix metalloproteinase-9 (MMP-9) of the two surgeries preoperatively and postoperatively.

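### The fluorescein staining score is summed over four zones although five are graded and the range is 0–15, and zones with exactly 5 or 10 stains have no grade

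*Protocol*

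**What the plan says.** Section 7.3.3 of the protocol defines the corneal fluorescein staining score, which is taken at baseline, 1 week and 1 month.

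- **Zones:** "Upper, lower, nasal, temporal and central quadrants were used". That is five areas, although they are called quadrants.
- **Grade per zone:** "Superficial punctate keratopathy (SPK) in the cornea was scored from 0 to 3 in each quadrant". Grade 0 is no staining, grade 1 is fewer than 5 stains, and grade 2 is more than 5 but fewer than 10. Grade 3 is more than 10, with the alternative "or filamentous staining detected".
- **Total:** "The total number was obtained by adding the scores of the four quadrants for each eye", with the range given in brackets as 0–15.

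Section 3.1 lists the measure in the primary objective: "corneal fluorescein (FL) staining, ocular surface disease index (OSDI) of the two surgeries preoperatively and postoperatively". The synopsis lists it too. The scoring rule is not restated or corrected anywhere else in the protocol.

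**The concern.** Section 7.3.3 is the operative instruction for turning a slit-lamp finding into a number, and it goes wrong in two unrelated places.

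1. The sentence that defines the total names a different number of zones from the sentence that lists them, and it does not fit the range printed beside it. Someone who builds a score sheet or a database sum from that sentence alone would get a total on another scale.
2. The grade boundaries are strict on both sides, so two stain counts belong to no grade. The assessor has to choose, and the protocol gives no rule for choosing.

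Staining is compared before and after surgery within each group, and between groups, in a study of 41 patients with one analysed eye each. In a sample of that size, each measure needs a single definition that two people would apply in the same way. The protocol chose to fix the scoring here, so this is not a detail left for a later analysis plan.

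**Working it through.** **Inputs, all from section 7.3.3 unless noted**

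- Zones named: upper, lower, nasal, temporal, central = 5
- Maximum grade per zone: 3
- Zones said to be summed: 4
- Stated range of the total: 0–15
- Measures in the primary objective (section 3.1): 6 ocular surface measures + 6 tear mediators = 12

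**Check 1: the range of the total**

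Maximum total = zones summed × maximum grade per zone.

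| Reading | Calculation | Range | Matches 0–15? |
|---|---|---|---|
| Four zones, as the sum sentence says | 4 × 3 = 12 | 0–12 | No |
| Five zones, as the list says | 5 × 3 = 15 | 0–15 | Yes |

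Totals of 13, 14 and 15 cannot occur under the four-zone reading. Two of the three statements (the list of zones and the range) agree with each other. Only the word *four* is out of line.

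**Check 2: whether every stain count has a grade**

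Zero stains is grade 0, so grade 1 is taken to start at one stain. For a zone without filaments:

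| Stains in the zone | Grade as printed |
|---|---|
| 0 | 0 |
| 1–4 | 1 |
| **5** | **none** |
| 6–9 | 2 |
| **10** | **none** |
| 11 or more | 3 |

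Counts from 0 to 39 were enumerated. Exactly two, 5 and 10, have no grade, and every other count has exactly one. A count of 5 could be read as grade 1 or 2, and a count of 10 as grade 2 or 3. Either way the zone moves by one point.

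**How the two checks relate**

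They are independent. The missing grades do not alter the range of the total, and correcting the number of zones does not supply the missing grades.

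**The case against.** The strongest reply is that the total explains itself. Five zones are listed, each is scored to 3, and the maximum is 15; a careful reader would see that *four* is a slip, and a natural one when the areas are called quadrants. This largely stands. It makes the intended sum fairly clear and lowers the severity. It does not remove the contradiction, because the wrong word is in the very sentence that tells the assessor what to add.

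The reply does not reach the grade boundaries. Nothing in the text shows which side 5 and 10 belong to. One caution applies: this part rests on the inequality signs as they read in the available text, and the scale is not repeated elsewhere for comparison. A lost *or equal to* sign is possible, so the signs should be checked against the source document.

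A reader might also infer several stronger things that the protocol does not support:

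- **That the 0–15 score cannot be obtained at all.** It can, from the five listed zones. The missing grades play no part in the range.
- **That the central zone is left out.** The protocol never says that any zone is omitted, and it gives no zone map.
- **That totals are off by 3 or 5 points.** These are ceilings. Three points requires the unlikely four-zone reading and an omitted zone at grade 3. Five points requires all five zones to have exactly 5 or 10 stains. The protocol gives no staining distribution that would show how often either occurs.
- **That the comparison of the procedures is biased.** A boundary convention applied consistently would be the same in both groups. Bias from assessor discretion would need inconsistent grading related to the procedure. The protocol does not describe masking of assessors, but that is a separate matter and does not show that such grading occurs. Nor does it say how many assessors there are.
- **That staining is the primary endpoint.** It is one of 12 measures named together.

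**Conclusion.** The point holds as two separate wording faults in one scoring rule. The sum sentence gives a maximum of 12 against the stated 15, most probably because *four* was written for *five*. The grades as printed leave counts of exactly 5 and exactly 10 undefined, which is worth one point per affected zone.

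The size of any effect on results cannot be estimated, because the protocol does not say how often such counts arise or how the scores were in fact added. Sample size is not affected, since no calculation is based on this score. The conclusion on the zones rests only on the text of section 7.3.3; the conclusion on the boundaries also assumes that the inequality signs are as printed.

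This should be fixed, because a measure in the primary objective needs one reproducible definition and the correction is cheap. It does not rank as a must-fix: the intended total can be recovered from the section itself, and the boundary gap is confined to two counts.

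**What to change.** Amend section 7.3.3 in three respects:

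1. State that the total is the sum of all five zones (upper, lower, nasal, temporal, central), with range 0–15. Calling the areas zones would avoid the ambiguity.
2. Make the grades exhaustive by assigning 5 and 10 explicitly. One example is 0 = none, 1 = 1–4, 2 = 5–9, 3 = 10 or more or filamentous. The protocol does not show which side was intended, so the investigators should confirm the convention from the scale they actually used.
3. State that the same convention applies in both groups and at every visit.

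If eyes have already been scored, check the sheets. Where only four zones were added and all five zone scores were recorded, re-sum them. Do not assume that eyes can be regraded: section 7.3.3 mentions no stored staining images, unlike the breakup-time examination in section 7.3.4, which is recorded on video. Where neither zone scores nor stain counts were kept, document the convention that was used.

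The cost is a one-paragraph amendment, with the ethics committee approval that section 14.2 requires, and a check of completed score sheets.

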### **7.3.4 Noninvasive Tear Breakup Time (NI-BUT)**

Four IR diodes were set on the Keratograph 5 (Oculus, Wetzlar, Germany) and arranged in two pairs, located one above the other. The red ring illumination used for corneal topography was deactivated; this ensured a dark background for the examination. An illuminated ring pattern was then projected onto the cornea. At the start of the recording, the subject will be asked to blink his or her eyes three times and then to keep them open as long as possible. Irregularities in the reflected image will be observed closely. Special attention will be given to distortions and gaps in individual rings and the time such deviations from the original ring pattern took to occur. The examination will be recorded on video. This evaluation will be performed at baseline, 1 day, 1 week and 1 month after surgery.

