| DURATION OF SUBJECT PARTICIPATION AND DURATION OF STUDY | 
Subjects will be on study for up to 2 months
 
Screening: 2-4weeks
 
Treatment: 1day
 
Follow-up: 1day, 1week and1month (1 month in total)
 
The total duration of the study is expected to be 9 months.
                                                                                                                                                                                                                                                                                                                                                                                                                                                                                                                                                                          |
| STATISTICS PLAN                                         | 
Data were analyzed using SPSS 19.0 software (SPSS, Chicago, IL, USA). Paired samples t-test (normally distributed data) or Wilcoxon test (non-normally distributed data) was used to determine significant differences between pre- and post-operative measurements in each group. Comparisons between the two groups were performed by Independent samples t-test (normally distributed data) or Mann-Whitney U test (non-normally distributed data). Pearson or Spearman rank correlation was used to analyzed for the correlations between tear inflammatory mediators and ocular surface parameters. P value of less than 0.05 was considered statistically significant. Data are presented as mean <math>\pm</math> SD.
                                                                   |

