## **2 STUDY RATIONALE**

This first all-in-one FS-laser system was designed to perform the refractive lenticule extraction (ReLEx) procedures, femtosecond lenticule extraction (FLEx) and small-incision lenticule extraction (SMILE). In FLEx, a corneal flap is created by the FS laser (similar to LASIK) and lifted, allowing lenticule removal[1-3]. For SMILE, a truly flapless procedure, only a small—2-4mm—incision is made, through which the lenticule is removed. Multiple etiologies contribute to this ocular surface disruption, including the flap creation and stromal ablation involved in previous refractive surgery techniques, such as: disable tear film, damage of the corneal nerve and postoperative inflammatory mediator. For both FLEx and SMILE, stromal ablation has been replaced by refractive lenticule removal. In terms of corneal flap formation, FLEx still requires an epithelial-stromal flap, while SMILE employs only a small incision to extract the lenticule. Hence, we hypothesize that SMILE will have less effect on patients' ocular surface markers and inflammatory mediators, compared to FLEx. To test our hypothesis, we conducted a prospective clinical study in patients who underwent FLEx or SMILE. Ocular surface parameters and inflammatory mediators were assessed and compared between the different types of surgery.

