## **4 STUDY DESIGN**

This is a single center, prospective and non-randomly study. 41 patients are planned to be enrolled. They are divided into two groups. One group will undergo the FLEx surgery, the other group will undergo the SMILE surgery. The ocular surface parameters and concentration of tear inflammatory mediators will be assessed at baseline, 1 day,1 week and 1 month postoperatively. Subjects who meet all inclusion criteria and none of the exclusion criteria will be entered into the study.

1. Minimum age of 18 years(range from 18 year to 25 years).
2. Corneal thickness more than 500  $\mu\text{m}$  and calculated residual stromal bed after treatment greater than 300  $\mu\text{m}$ .
3. Corneal thickness more than 500  $\mu\text{m}$  and calculated residual stromal bed after treatment greater than 300  $\mu\text{m}$ .
4. Preoperative cylindrical equivalent refraction between -0.25 D and -1.50 D.
5. Preoperative corneal curvature from 41.0 D to 46.0 D with a regular topographic pattern.

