### **7.3.5 Tear Meniscus Height (TMH)**

The subject will be asked to blink his or her eyes once, then the image of tear meniscus height will be captured by a Keratograph 5 (Oculus, Wetzlar, Germany). After that tear meniscus height will be measured at the centre of the lower lid margin. This performance will be taken three times and the average value will be recorded. This evaluation will be performed at baseline, 1 day, 1 week and 1 month after surgery.

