## **11. ADMINISTRATIVE, ETHICAL, REGULATORY CONSIDERATIONS**

The study will be conducted according to the Declaration of Helsinki. To maintain confidentiality, all laboratory specimens, evaluation forms, reports and other records will be identified by a coded number and initials only. All study records will be kept in a locked file cabinet and code sheets linking a patient's name to a patient identification number will be stored separately. Clinical information will not be released without written permission of the subject. The Investigator must also comply with all applicable privacy regulations .

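### No masking of the reader to procedure or visit is specified for NI-TBUT and tear meniscus height, two observer-dependent outcomes in a non-randomised study with a directional hypothesis

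*Protocol*

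**What the plan says.** Section 3.1 of the Protocol lists NI-TBUT and TMH among the outcomes of the primary objective.

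- **NI-TBUT (section 7.3.4).** A ring pattern is projected onto the cornea and "Irregularities in the reflected image will be observed closely". Attention goes to distortions and gaps in the rings and to when they appear. The section adds: "The examination will be recorded on video". It names no reader, no automated threshold and no scoring rule. It does not say whether the value is taken live or from the recording.
- **TMH (section 7.3.5).** A Keratograph image is captured. "After that tear meniscus height will be measured at the centre of the lower lid margin". Three takes are averaged. Neither the measuring tool nor the reader is described.
- **Design (section 4).** "This is a single center, prospective and non-randomly study", and "41 patients are planned to be enrolled". The split between the groups is not given.
- **Hypothesis (section 2).** "Hence, we hypothesize that SMILE will have less effect on" ocular surface markers and inflammatory mediators than FLEx.
- **Coding (section 11).** Specimens, forms and other records "will be identified by a coded number and initials only". The stated purpose is confidentiality.

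No section masks any assessor to procedure or visit.

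**The concern.** Deciding when a ring first distorts involves judgement. Placing a height measurement on an image probably does too. A reader who knows the procedure and the study's expectation may, without intending to, resolve doubtful cases in favour of that expectation. The resulting shift differs between groups, so it enters the group comparison directly. Neither averaging three takes nor adjusting for baseline covariates removes it.

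In a non-randomised study the group comparison is already open to confounding, which is hard to cure. Reader expectation is a second source of bias and is cheap to reduce, because the plan already records a video and captures an image. It also has to be settled in the protocol: a later analysis plan cannot mask values that were read with knowledge of the group.

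**Working it through.** **Is masking provided anywhere?** Sections 7.3.4 and 7.3.5 describe equipment, patient instructions and visits, but not the reader. Section 7 says that one surgeon operates and that one eye per subject is chosen at random for analysis; neither concerns the reader. Section 11 puts a number and initials on records. That keeps identity confidential, but it does not hide procedure or visit from staff who examine the patient at a known visit. So no masking is specified.

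**Is masked reading feasible?** For NI-TBUT the video exists under the current plan. For TMH the image is captured before it is measured, so reading can be separated from the visit as long as the image is kept.

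**How large could the effect be?** The protocol gives no effect size, SD, power or estimate of reader error, so there is no figure of its own to reproduce. What follows only illustrates sensitivity.

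Inputs:
- N = 41 (section 4). Assumed split 20/21, with 10/31 as an uneven alternative.
- Independent-samples t-test; a *P* "value of less than 0.05 was considered statistically significant" (synopsis, statistics plan). Two-sided testing is assumed.
- True group difference 0. Assumed between-group reading shift b = 0.2, 0.3 or 0.5 SD.

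Formulas: degrees of freedom = 41 − 2 = 39; critical value c = 2.023; noncentrality = b / √(1/n₁ + 1/n₂); rejection rate = P(|T| > c), with T noncentral t.

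For 20/21, √(1/20 + 1/21) = 0.3124, so an observed difference of 2.023 × 0.3124 = 0.63 SD is just significant. For 10/31, √(1/10 + 1/31) = 0.3637 and the threshold is 0.74 SD.

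| Assumed shift b (SD) | Noncentrality, 20/21 | Rejection rate, 20/21 | Noncentrality, 10/31 | Rejection rate, 10/31 |
|---|---|---|---|---|
| 0 | 0 | 5.0% | 0 | 5.0% |
| 0.2 | 0.64 | 9.6% | 0.55 | 8.4% |
| 0.3 | 0.96 | 15.5% | 0.82 | 12.7% |
| 0.5 | 1.60 | 34.5% | 1.37 | about 27% |

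These rates are per outcome and visit. Nearly all the rejections fall on the side of the shift: at 0.3 SD with 20/21, 15.3 of the 15.5 percentage points. If masking removed the shift entirely, the rate would return to 5% as far as reader expectation is concerned. Confounding would be unaffected.

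**The case against.** Several objections have force.

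- **The protocol is silent.** A reader might infer that staff who know the procedure take these readings openly, judging stored video by eye. The text does not say so. It names no reader and does not say what the reader knows. It mentions the video without saying that NI-TBUT is scored from it. For TMH, reading by eye is an inference. What stands is that masking is not specified.
- **Direction.** It is tempting to say that reader bias must always favour SMILE. The protocol predicts only less effect. It does not say whether surgery should raise or lower TMH, and postoperative drops are in use during follow-up. The direction is plausible for NI-TBUT but does not follow from the text for TMH.
- **Size.** The rejection rates only restate the assumed shifts and splits. They are not evidence that a shift of any given size would occur.
- **Existing coding.** Labels limited to a number and initials may already keep procedure off the records. The mediators are also quantified by software against standard curves, so the documents give no ground for extending this point to the tear assay. For NI-TBUT and TMH, however, such labels do not mask someone who knows the patient, and initials help identify the patient.
- **Incomplete masking.** A reader who ran the examination may remember a patient, and a ring image might reveal a flap. The documents do not settle either matter. Coding and random order reduce knowledge of group and visit without guaranteeing its absence.
- **Narrow scope.** The change covers two of the twelve measures in the primary objective (six ocular surface, six mediators). That limits the benefit but is no reason to forgo it.

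**Conclusion.** The point holds as a gap in safeguards. Two primary-objective outcomes have observer-dependent readings, and the protocol specifies no masking of the reader in a non-randomised comparison with a stated expectation. Reader expectation could therefore add to or mimic a group difference. The documents show neither that this bias will occur nor how large it would be. The range of about 10% to 35% false rejections per comparison depends wholly on assumed shifts of 0.2 to 0.5 SD, the 20/21 split and two-sided testing. The change is worth making because the material needed for masked reading is already produced. If the device determines a reading without an observer, the concern falls away for that outcome, but the protocol should then say so.

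**What to change.** In sections 7.3.4 and 7.3.5, state that:

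- the analysed NI-TBUT and TMH values are read from the recorded videos and captured images, which are kept for this purpose;
- the files are exported under a code that shows neither patient, procedure nor visit;
- the existing study reader reads them in random order;
- the code is broken only after the readings are locked.

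If either reading is fully automated by the device, state that instead. Report corneal sensitivity and fluorescein staining as unmasked outcomes.

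The cost is a file-coding step and a short delay before values are available. No extra staff, visit or procedure is needed, and sample size and significance level are unchanged. Masking stays incomplete if the reader recalls a patient or the image reveals the flap, and confounding from non-random allocation remains and must be handled separately.
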